## **4. STUDY POPULATION**

### **4.1 Sample Size Calculation**

A sample size of 330 women (165 per group) is required to provide 90% power to detect a difference of 20 points in the PFIQ-7 score at 18 months, assuming a standard deviation of 50, two-sided alpha of 0.05, and 20% loss to follow-up. In order to detect this standardised effect size of 0.4 SDs (20/50 points), 132 women will need to be recruited per group, or 165 per group to allow for dropout. Since the identified centres each see approximately 35 women a month for pessary care, we aim to recruit two to three women per month per centre.

The aim is to recruit a sample size sufficient to detect a 20-point difference in the PFIQ-7 score (the potential range of the PFIQ-7 is 0 to 300), although we acknowledge that an appropriate minimum clinically important difference for PFIQ-7 has not been formally determined. Barber et al. (2005) suggested a minimum clinically important difference (MCID) of 36 points, but it was emphasised that this was based on a small sample and applies only to within-group rather than between-group differences. Therefore, as part of the internal pilot, we will canvass PPI, investigators, and other participating clinicians to gauge the perceived importance of a 20-point difference.

Two recent trials which have used PFIQ-7 in populations of women using pessaries have reported SDs at 12 months and 24 months between 25 and 40 (Weigersma et al., 2014; Panman et al., 2016). These studies however were relatively small, conducted in only a few centres, and neither measured PFIQ-7 at 18 months. Given this uncertainty, a conservative assumption that the SD may be as high as 50 has been made. This will be monitored by examining the variability in the PFIQ-7 score for those women recruited in the internal pilot and we will continue to monitor the aggregated (blinded) SD regularly (every 40 cases using six-month outcome data; and as cases complete at 18 months), with a view to re-estimating the sample size at an appropriate point if required.

A sample size of 330 also provides power for the analysis of secondary outcomes, e.g. we will have more than 90% power (2-sided 5% level of significance) to detect a 20% difference in pessary use continuation rate (assuming at least 50% in the standard care group continue to use a pessary at 18 months).

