## 8 PROPOSED ANALYSES

### 8.1 Quantitative data analysis

All analyses will be conducted according to a pre-specified statistical analysis plan. All outcomes will be described with the appropriate descriptive statistics where relevant: mean and SD for continuous outcomes (or medians and interquartile range for skewed data), and counts and percentages for dichotomous and categorical outcomes.

The main effectiveness analysis will be based on the ITT principle. The analysis of the primary outcome will estimate the mean difference (with 95% confidence intervals) in the PFIQ-7 score at 18 months between the self-management and standard care groups using a mixed effects repeated measures model (which assumes incomplete outcome data to be missing at random). The model will incorporate PFIQ-7 scores at baseline, 6, 12 and 18 months, with age (<65/≥ 65) and pessary user type (new/existing) as fixed effects and recruitment centre as a random effect. Missing baseline data will be imputed. The repeated measures model will also estimate mean differences in PFIQ-7 at six and 12 months. Statistical significance will be at the 5% level.

The missing at random assumption for primary outcome data will be assessed further in sensitivity analyses. Treatment effects will be estimated under varying assumptions of data being missing not at random using pattern-mixture models. A complete case analysis will also be conducted.

Secondary outcomes will be analysed using an appropriate generalised linear model (for example binary logistic regression for dichotomous outcomes such as discontinuation with pessary (Y/N), and ordinal logistic regression for ordered categorical outcomes such as women's global impression of improvement (PGI-I). All models will be adjusted for minimisation covariates (age, pessary user type and centre) and baseline score (where applicable).

Given the potential for crossover, we will conduct a secondary analysis of compliers to estimate the effect of receiving the self-management intervention, using complier average causal effect (CACE) estimators. The CACE analysis will take a maximum likelihood approach, which can assume incomplete data to be missing at random, and can be adjusted for covariates. This analysis will provide unbiased effect estimates of receiving the self-management intervention, which will complement the unbiased ITT effect estimates of being offered self-management.

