## **4. STUDY POPULATION**

### **4.1 Sample Size Calculation**

As the primary outcome measure (PFIQ-7) remains unchanged then the sample size calculation for the original trial still applies to the long term follow up. We will conduct an intention to treat analysis including all 340 randomised participants, with imputed values for non-respondents, which will provide more than 90% power based on our original assumptions regardless of response rate at 4 years. If 264 women respond out of the 292 women who have consented to be approached at 4 years (90% response rate), then an observed cases analysis will also have 90% power (with two-sided alpha of 5%) to detect a difference in means of 20 points on the PFIQ-7 between the standard care and self-management groups, assuming a standard deviation for PFIQ-7 at 4 years of 50. We anticipate a high response rate given the current levels of retention, however a response rate of at least 65% would still provide more than 80% power in an observed cases analysis.

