## **8 PROPOSED ANALYSES**

### **8.1 Quantitative data analysis**

All analyses will be conducted according to a pre-specified statistical analysis plan, in line with the original trial plan. All outcomes will be described with the appropriate descriptive statistics where relevant: mean and SD for continuous outcomes (or medians and interquartile range for skewed data), and counts and percentages for dichotomous and categorical outcomes. The IPAQ-E is an adaptation

of the International Physical Activity Questionnaire (IPAQ) and is suitable when participants include those aged 70 years or more. IPAQ-E data will be scored for all respondents using the same method as the original IPAQ with the number of MET minutes calculated in each case (Forde 2018). A MET (metabolic equivalent of task) is a standard unit of estimated resting energy expenditure. The mean number of MET minutes will be compared between randomised groups, using a linear mixed model adjusting for minimisation variables. Data will also be summarised according to the standard IPAQ categories of low, medium and high physical activity.

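### The 4-year annex claims more than 90% power whatever the response rate because non-respondents are imputed; under any valid missing-data method the power falls as responders are lost

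*Protocol*

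**What the plan says.** Appendix D, 4.1 carries the original sample size reasoning over to the 4-year follow-up. It then makes two kinds of power statement.

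- For the intention-to-treat analysis of all 340 randomised women, with imputed values for non-respondents, it promises a level "which will provide more than 90% power based on our original assumptions regardless of response rate at 4 years".
- For the observed-cases analysis it lets power depend on response. If 264 of the 292 women who consented to be approached reply (90%), power is 90% "to detect a difference in means of 20 points on the PFIQ-7 between the standard care and self-management groups". The SD is again taken as 50. A response of at least 65% is said to leave more than 80%.

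The original assumptions are in the main protocol, 4.1: "A sample size of 330 women (165 per group) is required to provide 90% power to detect a difference of 20 points". The inputs behind that figure are listed in the same sentence: "assuming a standard deviation of 50, two-sided alpha of 0.05, and 20% loss to follow-up". They contain no correlation with earlier scores.

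Appendix D, 8.1 names no imputation method. It says "All analyses will be conducted according to a pre-specified statistical analysis plan, in line with the original trial plan". In the main protocol, 8.1, the primary outcome is analysed with a "mixed effects repeated measures model (which assumes incomplete outcome data to be missing at random"), and missing baseline data are imputed.

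**The concern.** Filling in a missing score does not create an observation. What a valid method knows about a non-respondent is what her earlier scores predict, and the rest of her 4-year outcome stays unknown. The standard error must carry that uncertainty, so power must fall as response falls. The annex accepts this for observed cases and denies it for the imputed analysis of the same women.

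PFIQ-7 remains the primary outcome at 4 years and this is the intention-to-treat analysis, so the claim sets how a result will be read. A null finding with 190 or 146 responders could be presented as coming from a study with more than 90% power when its power was materially lower. Response is also uncertain. Women must opt in to the 4-year questionnaire, and Appendix E expects somewhat lower retention than in the first stage.

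**Working it through.** **Inputs.** Difference 20, SD 50, hence d = 20/50 = 0.4; two-sided 5%; 340 randomised, taken as 170 per arm; 292 consented, 264 expected responders (all Protocol, 4.1 and Appendix D, 4.1). Assumed, because the protocol is silent: correlation rho between the 4-year score and earlier PFIQ-7 scores of 0, 0.6 or 0.8; responders split equally between arms; missingness unrelated to the outcome.

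**Step 1, the plan's own figures.**

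- Per group, n = 2(1.960 + 1.282)²/0.4² = 131.3, so 132. Allowing for 20% loss, 132/0.8 = 165, or 330 in total. This agrees with the protocol.
- 264 responders: 90.1% by the normal approximation, 89.9% by the noncentral t. This agrees.
- 65% response: 190 of 292 gives 78.7% (normal), and 221 of 340 gives 84.5%. The statement of more than 80% therefore depends on a denominator the annex does not make explicit. This is a side point.
- 340 women all observed: noncentrality 0.4 × √(170/2) = 3.69, power 95.7%. This is the only route by which the 340 women as such yield a figure clearly above 90%, and it treats every outcome as observed.

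**Step 2, power when some outcomes are missing.** With r = responders/340, a valid method has the precision of

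n_eff per arm = 170 / [(1 − rho²)/r + rho²]

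observed women. At rho = 0 this is simply the responders per arm. Example with 190 responders and rho = 0.6: r = 0.559; (1 − 0.36)/0.559 + 0.36 = 1.505; n_eff = 170/1.505 = 112.9; power 84.9%.

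| 4-year responders | rho = 0 | rho = 0.6 | rho = 0.8 |
|---|---|---|---|
| 340 | 95.7% | 95.7% | 95.7% |
| 264 (90% of 292) | 89.9% | 92.2% | 93.8% |
| 190 (65% of 292) | 78.3% | 84.9% | 90.0% |
| 146 (50% of 292) | 67.0% | 76.9% | 85.5% |
| 88 (30% of 292) | 45.8% | 58.4% | 73.0% |

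Reaching 90% takes about 265 responders at rho = 0, 236 at 0.6 and 190 at 0.8.

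**Step 3, simulation check.** 170 per arm, 2,500 runs per cell, 20 imputations from a regression on arm and one earlier score, Rubin's rules with small-sample degrees of freedom. Power of multiple imputation at rho = 0, 0.6 and 0.8:

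- 264 responders: 90%, 91%, 94%
- 190: 76%, 84%, 90%
- 136: 60%, 71%, 82%
- 68: 33%, 43%, 59%

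Type I error stayed at 4-6%.

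**Step 4, what would make the sentence true.** Deterministic single imputation, with predicted values analysed as if observed, kept power at 89-96% in every cell. Its type I error at 264, 190, 136 and 68 responders was 13%, 28%, 44% and 70% at rho = 0, and 8%, 12%, 17% and 28% at rho = 0.8. A single random draw per missing value did not hold 90% (92%, 85%, 79%, 75% at rho = 0) and also exceeded 5% type I error.

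**The case against.** Several points on the other side stand.

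- Imputation is not worthless. Baseline, 6-, 12- and 18-month scores are available and can recover part of the loss: at 190 responders, power rises from 78% to 90% as rho goes from 0 to 0.8. With high response, more than 90% is validly reached: 92.6% with 292 responders at rho = 0, or 92.2% with 264 at rho = 0.6. What fails is the claim that this holds at any response.
- The annex expects a high response and gives 65% as its lower case. Between 65% and 90% of 292, valid power is about 78-94%. The rows for 146 and 88 lie beyond what it anticipates, although the sentence as worded covers them.
- The annex does not neglect response. It keeps the Section 5.4 reminders, adds a pre-notification sub-study, and gives response-dependent power for observed cases.
- All 340 women were randomised before the annex was written, so the sentence fixes no sample size or stopping rule.

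Three stronger readings are tempting and are not supported.

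- A reader might infer that the 4-year analysis will have an inflated type I error. No passage plans single imputation; the annex names no method and refers to an analysis plan not shown here. The error rates in Step 4 show what the claim would require, not what is intended.
- A reader might infer that 340 − 292 = 48 women cannot respond. Appendix D, 5 says all participants who had not withdrawn at 18 months will be approached, so this is not established.
- A reader might infer that imputing abandons the original mixed model. Imputed outcomes can still be analysed with that model, and under missing at random with the same variables the two approaches have about the same precision.

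**Conclusion.** The power statement for the imputed analysis is wrong as written. On the original assumptions, which include no correlation with earlier scores, power falls below 90% once there are fewer than about 264 responders. With correlations up to 0.8 it is about 90-94% at 264 responders, 78-90% at 190, 67-86% at 146 and 46-73% at 88. No correlation tried makes it independent of response.

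The sizes rest on the protocol's difference and SD, equal response in both arms, missingness unrelated to outcome, and an assumed correlation range. Earlier scores are credited here with recovering missing information, not with reducing residual variance through baseline adjustment. Such adjustment would raise the figures, but they would still fall with response.

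At the hoped-for 264 responders the stated level is about right. The error bites when response falls short, which is exactly the case the sentence claims to cover.

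**What to change.** In Appendix D, 4.1, remove the claim that power does not depend on response. Deleting only the words from regardless onwards is not enough, because an unconditional figure above 90% would remain. Replace it with text such as: Power of the intention-to-treat analysis depends on the number of 4-year responders. For a 20-point difference, SD 50, two-sided 5% and a correlation with earlier PFIQ-7 scores between 0 and 0.8, it is about 90-94% with 264 responders, 78-90% with 190 and 67-86% with 146.

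If the trial's own 18-month data give a correlation between successive PFIQ-7 scores, use it to narrow the range. State whether response percentages refer to 292 or 340.

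Add that any imputation will use a valid variance method: multiple imputation with Rubin's rules, or the likelihood-based mixed model of 8.1. Either is acceptable.

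The cost is a few sentences and a less favourable stated power. No extra women or data are needed.

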## **5 PARTICIPANT SELECTION AND ENROLMENT**

All TOPSY participants who have not withdrawn from the study at the 18-month study time-point will be eligible and will be approached for follow up. All women who have participated in the TOPSY trial will be sent a summary of results newsletter from April 2022. Women were informed they would get this summary of results newsletter in the original participant information leaflet for TOPSY. Alongside this newsletter, a summary results cover letter, patient information leaflet and expression of interest form will also be sent which will include additional information about the 4-year follow up outlining what women are being asked to do i.e. complete one further questionnaire. Women will be invited to opt in should they wish to receive the 4 year questionnaire by either completing and returning the expression of interest form via mail, email or phone call as detailed in the flowchart below. If a woman returns her expression of interest form indicating she would like to complete the 4 year questionnaire, this will be sent on the required date (4 years from when first randomised to the TOPSY study).

Our retention process is the same as that detailed in Section 5.4 with one addition. SWAT 86 has been added for those who OPT in to the 4 year follow up. The SWAT 86 protocol is included as Appendix E. In summary, TOPSY participants remaining in the study 2 weeks prior to the distribution

of their 4 year questionnaire will be randomised to receive a pre-reminder or not to receive a pre-reminder. The mode of delivery of the reminder will be matched to the chosen mode of delivery of the follow-up questionnaire (email for those choosing to respond electronically and post, via a letter, for those choosing to self-complete a hard-copy questionnaire. A more detailed protocol for this SWAT can be found as Appendix E.

#### **Appendix D, section 5**

#### **TOPSY Long term (4 year) Follow-Up Participant Selection and Enrolment**

[figure not shown]

## **7. DATA COLLECTION**

### **Section 7.1 in the protocol describes the data collected during TOPSY.**

The first woman was randomised to TOPSY in May 2018, so the 4-year follow-up will commence in May 2022 and continue to October 2023.

#### **Questionnaire Completion**

Women selected how they would like to complete the questionnaire booklet (paper or via an online link via email) at randomisation and in letters to women sent to outline changes as a result of COVID-19. Women will be given the opportunity to change their preference for mode of completion should they wish to..

#### **Outcome Measures**

All measures utilised at the 18 month follow up would continue to be used at the 4-year follow up. Combined with the existing 18 month measures these data will be used to answer the long term follow up research question.

**International Physical Activity Questionnaire modified for the elderly (IPAQ-E)** (Hurtig-Wennlof et al, 2010) will be used to find out about the physical activities that people do as part of their everyday lives. The four questions ask about the amount of time in days and minutes, people spend sitting, walking, doing moderate and vigorous physical activity in the last 7 days. As the mean age of the sample is 64 years (SD 11 years) the IPAQ-E for the older age groups seemed more appropriate.

### **Section 7.3 outlines the data collection for the health economic element of TOPSY**

For the 4 year follow up we will continue to ask about NHS resource use. These data will answer the cost-effectiveness elements of RQ1 along with the primary outcome measure and the EQ-5D 5L.

## **8 PROPOSED ANALYSES**

### **8.1 Quantitative data analysis**

All analyses will be conducted according to a pre-specified statistical analysis plan, in line with the original trial plan. All outcomes will be described with the appropriate descriptive statistics where relevant: mean and SD for continuous outcomes (or medians and interquartile range for skewed data), and counts and percentages for dichotomous and categorical outcomes. The IPAQ-E is an adaptation

of the International Physical Activity Questionnaire (IPAQ) and is suitable when participants include those aged 70 years or more. IPAQ-E data will be scored for all respondents using the same method as the original IPAQ with the number of MET minutes calculated in each case (Forde 2018). A MET (metabolic equivalent of task) is a standard unit of estimated resting energy expenditure. The mean number of MET minutes will be compared between randomised groups, using a linear mixed model adjusting for minimisation variables. Data will also be summarised according to the standard IPAQ categories of low, medium and high physical activity.

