## **5.2 Randomisation and web-based data management system**

Randomisation will be minimised by age (<65/65+ years), pessary user type (new users/ existing users) and centre and will utilise the existing proven remote automated computer randomisation application at the study CTU - the Centre for Healthcare Randomised Trials (CHaRT, a fully registered UK CRN clinical trials unit) in the Health Services Research Unit, University of Aberdeen. This randomisation application will be available as an internet based service, located within the TOPSY data management system.

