### 7.1.2 Validated secondary outcome measures

Several secondary outcomes will be collected as described below. Frequency of the collection of each outcome is shown in table 7.1.

**Euroqol (EQ-5D-5L)** (The EuroQol Group, 1990) will be used to measure participants' generic quality of life, complementing the primary outcome measure of condition-specific quality of life, and also providing data for the analysis of cost-effectiveness. The EQ-5D-5L is a two-part instrument. The first section, the EQ-5D descriptive systems contains five items: mobility, self-care, usual activities, pain/discomfort and anxiety/depression. The second part, the EQ-5D VAS, is a Visual Analogue Scale. Data will be collected at each time-point to give a complete profile of QALYs across the trial time-points, calculated using an area under the curve method (see section 8.3).

**PFDI-20** will measure the severity of prolapse-related symptoms. This was developed and validated in parallel with the PFIQ-7 (Barber et al., 2005). It contains 20 questions about the presence of bladder, bowel and pelvic symptoms, and how bothersome these are. There are three subscales (UDI-6, CRADI-8, POPDI-6), with each subscore ranging from 0-100 and a total score of 0-300.

**The Pelvic Organ prolapse/Urinary Incontinence Sexual Questionnaire (PISQ-IR)** (Constantine et al., 2017), will be used to assess women's sexual symptoms. It contains 20 items with a score ranging from 0 to 48.

**General Self Efficacy scale (GSE)** (Schwarzer and Jerusalem, 1995) will be used to assess a woman's general self-efficacy (hypothesised to be a moderator of quality of life). This is a ten item scale with score ranging from 10 to 40.

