### **7.3 Data collection for Economic Evaluation**

Economic evaluation will be conducted alongside the main trial. For both groups, the EQ-5D-5L will be completed as part of the participant questionnaires at baseline, six, 12 and 18 months (<http://www.euroqol.org/>) to allow for the calculation of QALYs. Resource use will be captured by a combination of routinely-collected health data and participant-completed questionnaires (see table 7.2).

Overall costs will be estimated by multiplying resource use by unit costs obtained from the appropriate sources including trial specific costs, NHS reference costs, Unit costs of Health and Social Care and the British National Formulary (BNF).

*Table 7.2 Resource use and outcome data collected for economic evaluation*

| Pessary Self-Management group                                                                                                                                                                    |                                                                                                                                            | Standard pessary care group                                                                                                                                           |                                                            |
|---------------------------------------------------------------------------------------------------------------------------------------------------------------------------------------------------------|--------------------------------------------------------------------------------------------------------------------------------------------|------------------------------------------------------------------------------------------------------------------------------------------------------------------------------|------------------------------------------------------------|

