### **Research question (RQ)**

This RQ is supportive of, and additional to, the original TOPSY trial. The long term follow up research question is:

- What is the longer term (4 years) clinical-effectiveness and cost-effectiveness of self-management of vaginal pessaries to treat pelvic organ prolapse, compared to standard pessary care on condition specific quality of life?

All women in TOPSY completed a series of outcome measures combined into one questionnaire at baseline, 6, 12 and 18 months. The questionnaire booklet for the 4-year follow up will contain the same series of outcome measures as the 18 months booklet with the addition of some questions about pessary use between 18 months and 4 years and the IPAQ-E questionnaire as a measure of physical activity.

The sections below are extracts from the main protocol and outline the updated sections within that original protocol (version 7, 23rd November 2020). These changes will apply to the 4-year follow up. They are documented here for clear identification of the additions.

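### The 4-year IPAQ-E comparison adjusts only for the minimisation variables, with age cut at 65; exact age and baseline EQ-5D-5L are already held and would add some precision at almost no cost (minor).

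*Protocol*

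**What the plan says.** Appendix D adds to the 4-year booklet some questions on pessary use "and the IPAQ-E questionnaire as a measure of physical activity". Table 7.1 of the main protocol does not list IPAQ-E at baseline, 6, 12 or 18 months. Its analysis is given in one sentence of Appendix D, section 8.1: "The mean number of MET minutes will be compared between randomised groups, using a linear mixed model adjusting for minimisation variables".

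Section 5.2 defines the minimisation variables: "Randomisation will be minimised by age (<65/65+ years), pessary user type (new users/ existing users) and centre". The primary model in section 8.1 of the main protocol enters age in the same two classes: "with age (<65/≥ 65) and pessary user type (new/existing) as fixed effects and recruitment centre as a random effect". For secondary outcomes the general rule there is: "All models will be adjusted for minimisation covariates (age, pessary user type and centre) and baseline score (where applicable".

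Two further baseline items are available. Appendix D, under Outcome Measures, reports a mean and SD of age ("As the mean age of the sample is 64 years (SD 11 years"), so age is held in years and not only as a class. Section 7.3 says that "the EQ-5D-5L will be completed as part of the participant questionnaires at baseline, six, 12 and 18 months", and section 7.1.2 describes its descriptive part as "five items: mobility, self-care, usual activities, pain/discomfort and anxiety/depression".

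**The concern.** When an outcome has its own baseline score, that score usually does most of the work in reducing residual variance. Here there is none, so the general rule reduces to two classes of age, two classes of user type, and centre. A two-class age variable is a coarse predictor of physical activity in a sample whose mean age lies one year from the cut. Baseline mobility and usual activities plausibly predict activity four years later, and the EQ-5D-5L index is already needed for the QALY calculation in section 8.3.

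What is at stake is the width of the confidence interval for the difference in mean MET minutes. No sample size or power is stated for IPAQ-E, so it takes whatever precision the respondents supply.

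**Working it through.** **The plan's own figures.** The only powered outcome is PFIQ-7: difference 20, SD 50, two-sided alpha 0.05, power 90% (section 4.1). The number per arm is 2 × (1.960 + 1.282)² × 50² / 20² = 131.4, rounded up to 132. Allowing for 20% loss, 132 / 0.8 = 165 per arm, or 330 in all. This agrees with the protocol. The 264 respondents in Appendix D, section 4.1 (132 per arm) give 90.1% power for PFIQ-7. No corresponding figure exists for IPAQ-E, so the gain is expressed below relative to the planned model.

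**Step 1: what the age cut keeps.** Inputs are mean 64, SD 11 and cut 65, with normality assumed.
- Standardised cut: c = (65 − 64) / 11 = 0.091.
- Share aged 65 or over: p = 0.464.
- Share of the linear R² of age that is kept: φ(c)² / [p(1 − p)] = 0.3973² / (0.464 × 0.536) = 0.63.

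**Step 2: exact age in place of the class.** If age has correlation r with MET minutes, the residual variance ratio is (1 − r²) / (1 − 0.635 r²), and the gain in effective sample size is its inverse minus 1.

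| Absolute r (assumed) | Variance ratio | Gain |
|---|---|---|
| 0.1 | 0.996 | 0.4% |
| 0.2 | 0.985 | 1.5% |
| 0.3 | 0.965 | 3.6% |
| 0.4 | 0.935 | 7.0% |

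**Step 3: exact age plus baseline EQ-5D-5L.** Let a and q be the absolute correlations of age and EQ-5D-5L with MET minutes, and ρ the size of the overlap between the two predictors (a negative correlation of age with EQ-5D-5L, 0 or 0.2 in size). Then R² = (a² + q² − 2ρaq) / (1 − ρ²), and the variance ratio is (1 − R²) / (1 − 0.635a²).
- Low end, a = 0.2, q = 0.2, ρ = 0.2: R² = 0.067; ratio 0.933 / 0.975 = 0.958; gain 4.4%; standard error 2.1% smaller.
- Middle, a = q = 0.3: ratio 0.901 (ρ = 0.2) to 0.870 (ρ = 0); gain 10.9% to 15.0%. A comparison with 80% power would have about 84% to 85%.
- High end, a = 0.3, q = 0.4, ρ = 0: R² = 0.25; ratio 0.75 / 0.943 = 0.795; gain 25.7%; standard error 10.8% smaller.

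On 264 respondents this is equivalent to about 276 (264 × 1.044) to 332 (264 × 1.257).

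**Limits of the check.** The calculation treats user type and centre as explaining the same amount under both models, and the relation of age to MET minutes as linear. The correlations are not in the protocol.

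**The case against.** The strongest reply is that the sentence is consistent. Section 8.1 of the main protocol adjusts for a baseline score only where there is one, Appendix D says its analyses follow the original plan, and a measure introduced years after randomisation cannot be given a baseline. Further covariates may also be named in a statistical analysis plan that is not shown. All of this stands as a defence against a charge of error. It does not answer the suggestion, because the annex states its covariate set and better covariates are already in the database.

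A second reply is that the gain is unproven. That is fair: exact age alone brings little, and the larger part rests on an unknown correlation between EQ-5D-5L and MET minutes. The annex also does not restate the age cut; it follows from section 5.2 and the primary model. If age in years were already intended, only EQ-5D-5L would be new, with a gain over the same assumed range of about 2% (a = 0.3, q = 0.2, ρ = 0.2: 0.890 / 0.91 = 0.978) to 21% (a = 0.3, q = 0.4, ρ = 0: 0.75 / 0.91 = 0.824).

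Three stronger readings are tempting and are not supported.
- *MET minutes are skewed, so means should give way to a rank-type or proportional-odds analysis.* The protocol gives no distribution for MET minutes; its provision of medians for skewed data concerns description. A raw-mean test kept about 5% type I error in lognormal simulations. Which method has more power depends on the shape of the effect. With 132 per arm, 7% zeros and a common ratio of 1.35 (log-SD 0.7, 1.0, 1.2), power for means against ranks was 80% v 83%, 45% v 53% and 28% v 40%. With the benefit confined to 15% of women it was 81% v 52%, 55% v 47% and 41% v 45%. All these inputs are assumptions. Section 8.1 also plans ordinal regression for ordered categories, not for continuous totals.
- *IPAQ-E is the only new outcome, or the only one without a baseline.* The 4-year booklet also adds pessary-use questions, and the Health Resource Questionnaire has no baseline entry in Table 7.1.
- *The cut throws away over a third of the information.* The 37% lost is a share of what age explains, not of the outcome variance.

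**Conclusion.** The point holds as a minor, nearly free improvement. The planned comparison is valid: the covariate set causes neither bias nor an inflated error rate. It gives up some precision by using age in two classes and leaving baseline EQ-5D-5L out when no baseline IPAQ-E exists.

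The size is about 4% to 26% in effective sample size, with a standard error about 2% to 11% smaller, if age correlates 0.2 to 0.3 and EQ-5D-5L 0.2 to 0.4 with MET minutes. Most of this comes from EQ-5D-5L. If the true correlations are near zero, the gain is negligible and little is lost by including the covariates. The 63% figure rests on approximate normality of age. Nothing here affects the primary outcome or the case for the 4-year follow-up.

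**What to change.** In the IPAQ-E sentence of Appendix D, section 8.1, keep the linear mixed model and the difference in mean MET minutes as the main comparison, and replace the adjustment set by: *centre, pessary user type, age in years (in place of the <65/65+ class) and baseline EQ-5D-5L index*. Add that missing baseline EQ-5D-5L values will be imputed, as section 8.1 of the main protocol already does for missing baseline data in the primary model. Make the same change in the statistical analysis plan before the 4-year data are analysed by group.

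The cost is wording only: no new data, no added burden on participants, and no change to the quantity estimated. The one extra task is the imputation rule for baseline EQ-5D-5L.
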